### Hospital Anxiety and Depression Scale – HADS

HADS is a self-administered questionnaire consisting of 14 items (each scored 0–3), seven of which concern depression and seven anxiety symptoms.^48^ One of the main purposes of this instrument was to identify affective symptoms among somatically ill patients.^49^ Therefore, the items focuses on the non-somatic aspects of depression and anxiety, to avoid that symptoms from the somatic disease, such as fatigue, affected the measurements.^48^ ^50^ Depression and anxiety items are summarized separately in two scales ranging from 0 to 21, where a higher score indicates more symptoms.

### Biomarkers

Several components in the inflammatory system may be associated with cardiovascular disease and atherosclerosis. A meta-analysis comprising 29 prospective studies associated interleukin-6 (IL6), tumor necrosis factor-alfa (TNF-alfa) and C-reactive protein (CRP) to increased cardiovascular risk independent of traditional risk factors in the healthy population.^51^

Fasting blood samples will be collected at baseline and follow-up for assessment of:

- Lipids (total-, low density lipoprotein, very low density lipoprotein, high density lipoprotein, cholesterol and triglycerides)
- Endocrine function (HbA1c, glucose, insulin, thyroid stimulating hormone)
- Kidney function (creatinine, eGFR)
- Haematology
- Inflammatory disease (hsCRP, hsTNT, orosomucoid, IL-6, TNF-alfa, adiponectine) biomarkers for later analysis

## Biological material

Two types of biobanks will be established

1. Research biobank for analysis of the material within the framework of the study.
2. Biobank for future research. The material can only be used with a renewed approval from the patients.

For every patient, 20 ml of the drawn 50 ml blood is stored in a biobank for biomarker analysis. Blood samples will be stored until the end of the study (last patient, last visit) plus five years and they will be destroyed thereafter. This will be registered in the Danish Data Protection Agency.

Serum, plasma and full blood will be stored in a -80^o^C fridge with an alarm mechanism that goes off in case the temperature rises above -60^o^C. The cryotubes are kept in 9x9 consecutively numbered boxes, separated as Serum, Plasma and Full blood. The content of each box is noted in an electronic file, coupling patient ID, box number and number of cryotubes.

# Statistics

## Sample size

The primary endpoint is change in microvascular function assessed by CFVR.

We wish to be able to detect a difference in change in CFVR between groups of 10%, equal to a change in CFVR of 0.24, assuming a baseline mean CFVR of 2.4. According to our previous study (22) the standard deviation of the within individual change is assumed to be 0.3. With power of 0.8 and two-sided significance level of 0.05, 26 patients should be included in each group. With 26 in each patient group we will be able to detect a moderate or larger effect on symptom burden. Anticipating dropout, randomization of a total of 60 patients was chosen. Dropout within the first three weeks of inclusion is replaced by new inclusion.

SAQ has four subscales each with a score from 1-100. We have not found data on within-study subject variation on SAQ. However, previous trials have obtained changes in SAQ of 10-20 points after intervention.^18^ ^46^ ^13^ A trial of 46 patients (predominantly women) with microvascular angina randomized to either ranolazine, ivabradine or placebo for four weeks found a SAQ score change of 10-40 points across different SAQ parameters, all highly significant (p<0.001).^18^ We will conduct a study on a similar study population, and we therefore expect to have the statistical power to document clinically relevant effects.

With 60 participants included, the probability is 80 percent that the study will detect a treatment difference at a two-sided 0.05 significance level, if the true difference between treatments is 11. This is based on the assumption that the standard deviation of the response variable is 15.

Analyses will be performed in STATA/IC 13.1. Categorical data will be presented as number (percentage), continuous data as mean (SD) or median (interquartile range) if normal distribution cannot be assumed. Regression analysis will be performed with the primary outcome change in symptoms (SAQ) and the independent variable change in CFVR.

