# Study design

The study is a randomized, controlled intervention trial. Patients from the iPower cohort fulfilling the inclusion criteria of this present study are invited to participate. Please see **figure 2** for a schematic overview of the inclusion. Details regarding the study information and informed consent are further described in the chapter “Ethical aspects”. Sixty participants are included in the study. After baseline examinations participants are randomized (1:1) to either comprehensive intervention for 24 weeks or usual care (controls). Baseline and 24-week assessments are performed at the Hospitals Bispebjerg and Frederiksberg. Please see **Table 1.**

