## Figure 4. Participants’ study plan

## Figure 5. Antihypertensive treatment algorithm

### Exercise training (ET)

ET consists of group sessions of aerobic interval training and resistance exercise, scheduled twice weekly throughout the 24-week intervention period. Each group consists of 10 participants and each session lasts for 1 h. The group sessions are supervised and monitored by a physiotherapist experienced in cardiac rehabilitation. The intensity of the training will be individually adapted to the concomitant weight loss program with restricted calorie intake. During the first 12 weeks of calorie restriction, the training will be modest in load and intensity and primarily consist of short aerobic interval sessions and resistance exercise of the large muscle groups.

Attendance at training sessions will be registered by the physiotherapist. Home based training is accepted, if participants cannot attend all the sessions. Compliance of home-based training is self-reported (registered by a telephone call to the participant). Lack of compliance is defined as < 50% attendance to training sessions/home training. Lack of compliance within the first five weeks of intervention will lead to withdrawal from the study and possibly new inclusion.

**Please see Figure 6** for an overview of the estimated timeline of the training sessions throughout the study period. The 30 participants in the intervention group attend at 3 teams of 10 participants.

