### Low energy diet (LED)

Weight loss will be achieved by following an evidence-based LED formula delivered by Cambridge Weight Plan. The diet, consisting of shakes, soups and bars, allows the participant to consume 800-1200 kcal/day. The diet contains the daily need of energy as well as macro- and micronutrients, proteins, essential fatty acids and recommended daily doses of vitamins and minerals^29^. The goal of the intervention is a total weight loss of at least 10% without significant loss of muscle mass.

Participants will be offered comprehensive support to fulfill the weight loss through a combination of two individual meetings and group sessions with a dietician. Attendance in a group session (5-7 participants and a dietician) defines the beginning of the 24-week interventional period for each participant. The purpose of this meeting is information about the LED treatment. Hereafter, participants are offered a single individual meeting with the dietician in order to register weight and dispense the Cambridge Weight Plan diet. Participants then follow a 12-week period with LED and attend group sessions every second week with their team and a dietician. The purpose of the group sessions is to motivate, adjust treatment to individual concerns, and monitor weight and compliance to intervention. During the 12^th^ week, participants will be offered another individual meeting with the dietician in order to motivate and advise in the weight maintenance diet.

The recommended weight maintenance diet is high in protein and with a low glycemic index modified from the DiOGenes study.^30^ Taking into consideration that the participants have CMD the high protein diet is adapted to resemble the Mediterranean diet, which is low in saturated fat (< 10%) and recommended to heart patients,^31^ with protein sources mainly from fish, poultry, egg, dairy, and vegetables. During the 12 weeks of weight maintenance the participants will be encouraged to still attend the monthly group sessions with the dietician. In case of weight gain LED can be used to replace meals. No weight loss within the first three weeks of LED is considered as lack of compliance and leads to withdrawal from the study.

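### The stated 80% power assumes that all women are independent, although the intervention arm alone is treated in shared groups for 24 weeks

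*Protocol*

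**What the plan says.** Allocation is by individual. According to Study design, "participants are randomized (1:1) to either comprehensive intervention for 24 weeks or usual care (controls").

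Only the intervention arm is then treated in groups. Exercise training (ET) says: "The 30 participants in the intervention group attend at 3 teams of 10 participants". Sessions run twice weekly for the whole 24 weeks under a physiotherapist. Low energy diet (LED) says: "Attendance in a group session (5-7 participants and a dietician) defines the beginning of the 24-week interventional period for each participant". The diet sessions continue with the same team, and their stated purposes include motivation and monitoring of weight and compliance. Controls – usual care describes no group activity.

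The Sample size section sets the CFVR target as a between-group difference in change "equal to a change in CFVR of 0.24, assuming a baseline mean CFVR of 2.4", with the assumption that "the standard deviation of the within individual change is assumed to be 0.3". It concludes: "With power of 0.8 and two-sided significance level of 0.05, 26 patients should be included in each group". It then adds: "Anticipating dropout, randomization of a total of 60 patients was chosen". For symptoms it says: "With 60 participants included, the probability is 80 percent that the study will detect a treatment difference at a two-sided 0.05 significance level", for a true difference of 11 and a standard deviation of 15. The section mentions no group, ICC or design effect.

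**The concern.** This is a partially nested design: grouped delivery in one arm, ungrouped women in the other. Women in the same group share sessions, peers and the pace of the programme, so their changes in weight, fitness, symptoms and possibly CFVR may be positively correlated. If so, the mean of the intervention arm is less precise than 26 or 30 independent women would make it, and the usual two-sample formula overstates power.

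The protocol describes the trial as a proof of concept meant to justify a multicentre trial. A reader who takes 80% at face value may put too much weight on a negative result. If group membership is not recorded, the question cannot be examined afterwards.

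**Working it through.** **Inputs from the protocol.** CFVR: difference d = 0.24, SD = 0.3, two-sided 5%, 26 per group needed, 60 randomised 1:1 (30 per arm). SAQ: difference 11, SD 15, 60 women (30 per arm). Three training teams of 10; diet groups of 5-7.

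**Assumption, not in the protocol.** The ICC of the outcome within a group: 0.01 to 0.10.

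**Step 1: reproduce the stated figures under independence.**
- CFVR, normal approximation: n = 2 × [0.3 × (1.960 + 0.842) / 0.24]² = 24.5, so 25 per group. The two-sample t-test needs 25.5, so 26, as stated. Power at 26 per group is 80.7%; at 30 per group it is 86.1%.
- SAQ, t-test, 30 per group: power 79.8%, which matches the stated 80%.

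The protocol's arithmetic is right on its own inputs.

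**Step 2: allow for grouping in the intervention arm only.**
- Design effect: DE = 1 + (m − 1) × ICC, where m is the group size.
- Standard error of the arm difference: SE = SD × √(DE/n + 1/n).
- Power from the noncentral t with 2n − 2 degrees of freedom and noncentrality d/SE.

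With 26 completers split 9, 9 and 8, the size-weighted m is (81 + 81 + 64)/26 = 8.7. With 30 completers, m = 10.

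Worked example, CFVR, 26 per arm, ICC 0.05:
- DE = 1 + 7.69 × 0.05 = 1.385
- SE = 0.3 × √(1.385/26 + 1/26) = 0.0909, against 0.0832 under independence
- d/SE = 0.24/0.0909 = 2.64, against 2.88
- power = 73.6%, against 80.7%

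Worked example, SAQ, 30 per arm, ICC 0.05:
- DE = 1 + 9 × 0.05 = 1.45
- SE = 15 × √(1.45/30 + 1/30) = 4.29, against 3.87
- d/SE = 11/4.29 = 2.57, against 2.84
- power = 71.3%, against 79.8%

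| Assumed ICC | CFVR, 26 per arm | CFVR, 30 per arm | SAQ, 30 per arm |
|---|---|---|---|
| 0 | 81% | 86% | 80% |
| 0.01 | 79% | 85% | 78% |
| 0.02 | 78% | 83% | 76% |
| 0.05 | 74% | 79% | 71% |
| 0.10 | 67% | 72% | 64% |

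**Step 3: take the diet group as the cluster instead.** For CFVR at 26 per arm and ICC 0.05:
- Five groups: m = 26/5 = 5.2, DE = 1.21, power 77%.
- Six groups (the number costed in Table 3): m = 26/6 = 4.33, DE = 1.17, power 78%.

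These powers treat the ICC as known. They make no deduction for having to estimate it from so few groups.

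**The case against.** The case on the other side has real force.

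- **No stated figure is miscalculated.** This stands. The flaw is an unstated assumption, and the size of any loss rests on an ICC that the protocol does not give. At 0.02 or below, the loss for CFVR is at most about three points.
- **Thirty per arm give a cushion.** This stands in part. With 30 completers, CFVR power is still about 79% at ICC 0.05. But the extra women are there for dropout, and the SAQ figure already uses all 60.
- **Correlation may be weak.** Home training is accepted when sessions are missed, medication and two dietician meetings are individual, and the follow-up CFVR reading is blinded. All this may lower the ICC; none of it shows that the ICC is zero. Blinded reading does not remove correlation from shared delivery, and SAQ is self-reported by unblinded women.
- **The cluster is not clearly defined.** This stands. Training teams number 10 women in the ET section but 8 in Table 3, and diet groups are smaller. Results should therefore be shown for both kinds of group.

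A reader might go further and infer that the trial's false-positive rate exceeds 5%. The protocol does not support that, because it names no test for the between-arm comparison. The one regression it specifies relates change in SAQ to change in CFVR, which is not the arm comparison. How the arms are compared may be settled in a statistical analysis plan that is not shown.

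A reader might also infer that team membership is fixed, that each team has its own instructor, or that season affects one arm only. The protocol says none of these, and allocation in small blocks would spread calendar effects over both arms.

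**Conclusion.** The point holds in a limited form. The 26 per group for CFVR and the 80% power for SAQ are correct under full independence. The protocol's own group delivery in one arm puts that condition in doubt, and the Sample size section does not mention it.

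At an ICC of 0.05, used here only as an illustration, power is about 74% for CFVR at 26 per arm and 71% for SAQ. Over ICC 0.01 to 0.10 the ranges are 79% to 67% and 78% to 64%. The loss shrinks if all 30 per arm complete or if the diet group is the relevant cluster, and it is negligible if the ICC is close to zero. This warrants a correction to the stated power, not a change to the size of the trial.

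**What to change.** Keep 60 women and make three changes.

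1. In the Sample size section, say that the power assumes independence within training teams and diet groups, and give it by ICC. For example: with 26 per group, CFVR power is 81% if outcomes are independent within teams, and about 79%, 78%, 74% and 67% at ICCs of 0.01, 0.02, 0.05 and 0.10; for SAQ with 30 per group it is 80% under independence, and about 78%, 76%, 71% and 64%. Label the ICCs as assumptions.
2. Record each intervention woman's training team and diet group in the case record. The physiotherapist already registers session attendance, but the protocol does not say that membership is captured. Reconcile the team size in the ET section with Table 3.
3. Report a sensitivity analysis of the between-arm CFVR and SAQ comparisons in which the intervention-arm variance is multiplied by 1 + (m − 1) × ICC, for ICC from 0.01 to 0.10. Fixed ICC values are preferable here because three teams are too few to estimate one reliably. A random-effect model need not be the required analysis.

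The cost is a short addition to the text, two data fields and one extra analysis, with a slightly less favourable stated power. No extra patients, staff or procedures are needed.

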### Seattle Angina Questionnaire - SAQ

Improving quality of life is one of the primary goals in treating patients with stable angina pectoris. Quality of life is increasingly used as a patient-centered endpoint in cardiovascular disease studies, especially for stable ischemic heart disease. From a patient point of view angina may be the most important factor reducing quality of life, and data suggest that angina frequency predicts higher rates of cardiovascular events and death.^43^ Angina symptoms may not always be associated with an impaired CFVR, and conversely^44^ but interventions with ACE-I^18^ or weight loss ^45^ have improved angina symptoms (assessed by SAQ or Canadian Cardiovascular Society, CSS) and CFVR in previous studies.

The SAQ is a reliable, predictive tool that has been validated in 175 women with a confirmed diagnosis of stable coronary artery disease (CAD) and angina pectoris ^46^. It is a 19-item health-related quality-of-life measure for patients with coronary artery disease. The answers given by the patients in the SAQ’s questions are used to calculate scores in five scales:

- Anginal Stability: Whether a patient’s symptoms are changing over time.
- Anginal Frequency: Present frequency of symptoms.
- Physical Limitation: How much a patient’s condition is hampering her physical abilities.
- Treatment Satisfaction: How well a patient understands and what she thinks of it.
- Quality of Life: A measure of the overall impact of a patient’s condition on her interpersonal relationships and state of mind.

Scale scores are transformed to a 0-100 range by subtracting the lowest possible scale score, dividing by the range of the scale and multiplying by 100. Higher scores indicate less symptom burden. Because each scale monitors a unique dimension of coronary artery disease, no summary score is generated. A score change of 10 points is clinically perceptible to patients and is considered a clinically relevant difference, while a substantial change is considered to be a change of 20 points^47^ (please see Appendix for SAQ).

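### The protocol overstates power for the SAQ: 80% for 11 points needs all 60 women analysed, and the 10-point relevant difference has only about 65% to 72%

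*Protocol*

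**What the plan says.** The Sample size section of the protocol (under Statistics) sizes the trial on the primary endpoint, coronary flow velocity reserve (CFVR), and arrives at 26 women per group, 52 in all. It then makes three statements about power for the SAQ.

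- At the CFVR sample size: "With 26 in each patient group we will be able to detect a moderate or larger effect on symptom burden". Moderate is not defined, either in points or in SD units.
- At the number randomised: "With 60 participants included, the probability is 80 percent that the study will detect a treatment difference at a two-sided 0.05 significance level". The effect assumed for this is 11 SAQ points, and the SD is taken as 15, which the section labels an assumption.
- From changes seen in earlier trials, the authors conclude that they expect enough power to show clinically relevant effects.

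The section explains the step from 52 to 60 as an allowance for dropout, and says that dropouts in the first three weeks are replaced. The Randomization section says only that replacement is possible.

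On the scale itself, the section states: "SAQ has four subscales each with a score from 1-100. We have not found data on within-study subject variation on SAQ". The section on the Seattle Angina Questionnaire lists five scales, transformed to 0-100, without a summary score. It sets the benchmark: "A score change of 10 points is clinically perceptible to patients and is considered a clinically relevant difference". It calls 20 points a substantial change.

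**The concern.** The Sample size section works with two different numbers of women. The CFVR calculation needs 52 and keeps the other 8 in reserve for losses. The SAQ calculation counts those 8 as analysed. If the reserve is used up as foreseen, the SAQ power is lower than stated.

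The 11 points for which 80% is claimed also lie above the 10 points that the protocol treats as clinically relevant, yet the section ends by expecting power for clinically relevant effects. The sentence about a moderate effect cannot be checked, because the term has no value attached.

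The aim of the trial is improvement in both angina and microvascular function, so the SAQ carries half of the proof of concept. Someone who relies on the stated power could read a null SAQ result as stronger evidence against a relevant benefit than the design can give.

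**Working it through.** **Inputs**

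- Two-sided significance level 0.05 and 1:1 allocation (Sample size; Study design).
- SAQ difference 11 points and SD 15 (Sample size). The SD is an assumption, since the authors found no data on within-subject variation.
- Clinically relevant change 10 points (Seattle Angina Questionnaire section).
- n = 30 per group if all 60 are analysed, or n = 26 per group if the 60 - 52 = 8 reserve women (8/60 = 13.3%) are lost.

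**Method.** Two-sample t-test. For difference D and n per group, the noncentrality is D / (SD x sqrt(2/n)), with 2n - 2 degrees of freedom. Power is the probability that the noncentral t exceeds the two-sided 5% critical value. The normal approximation is given as a check.

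**Step 1: the protocol's own figures.** With n = 30, SD x sqrt(2/n) = 15 x 0.2582 = 3.873, so the noncentrality is 11/3.873 = 2.84. Power is 79.8% by the t-test and 81.1% by the normal approximation. The stated 80% reproduces. The CFVR size reproduces as well: 0.24/0.3 = 0.8 SD, and 26 per group gives 80.7%.

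**Step 2: the same calculation with 26 per group.** Now 15 x sqrt(2/26) = 15 x 0.2774 = 4.160, and the noncentrality is 11/4.160 = 2.64. Power falls to 73.7% (normal 75.3%).

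**Step 3: the 10-point benchmark.** The noncentrality is 10/4.160 = 2.40 with 26 per group and 10/3.873 = 2.58 with 30.

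| SD 15 | 26 per group (52) | 30 per group (60) |
|---|---|---|
| Power for 11 points, t-test (normal) | 73.7% (75.3%) | 79.8% (81.1%) |
| Power for 10 points, t-test (normal) | 65.4% (67.1%) | 71.9% (73.3%) |
| Power for 0.5 SD (7.5 points), t-test (normal) | 42.4% (43.8%) | 47.8% (49.1%) |
| Difference with 80% power, t-test | 0.79 SD = 11.9 points | 0.74 SD = 11.0 points |

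For 80% power at 10 points, 37 per group (74 women) would be needed: 36 gives 79.7% and 37 gives 80.8%.

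**Step 4: what moderate would have to mean.** With 26 per group, 12 points is 12/15 = 0.8 SD and has 80.7% power. At SD 15 the sentence is therefore true only if moderate means about 12 points or more. By the usual convention 0.79 SD is a large effect and 0.5 SD a medium one.

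**Step 5: sensitivity to the SD, 26 per group.** The values 12.5 and 20 are assumptions chosen on either side of 15.

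| SD | Power for 10 points | Difference with 80% power |
|---|---|---|
| 12.5 | 80.7% | 0.792 x 12.5 = 9.9 points |
| 15 | 65.4% | 11.9 points |
| 20 | 42.4% | 15.8 points |

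**The case against.** **The 80% figure is not an error.** A reader might infer that it was miscalculated. It was not: it reproduces for 60 women, and the protocol says openly that it refers to 60. The fault is only the mismatch with the dropout allowance, worth about 6 percentage points of power or 0.9 SAQ points. This stands.

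**Moderate need not mean 0.5 SD.** A reader might conclude that 26 per group cannot detect a moderate effect. The documents do not support this, because the 0.5 SD convention appears nowhere in them. The protocol's own benchmarks are 10 and 20 points, and an effect of about 12 points or more between them is detectable at SD 15. The fair criticism is that the term is undefined. This stands too.

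**Replacement could keep the number near 60.** Early dropouts are replaced. The Randomization section allows replacement without a time limit, the Exercise training section mentions possible new inclusion for non-compliance in the first five weeks, and Table 3 budgets 10 extra participants. This softens the dropout point but does not remove it. After three weeks replacement is possible and not promised, and the section itself gives dropout as the reason for 60. Nor does it help at 10 points, where even 60 evaluable women give only 72%.

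**The 10 points and the 11 points are different quantities.** The 10 points describe a score change that patients perceive, and the 11 points a difference between group means. They do not contradict each other. The expectation of adequate power also rests on cited changes of 10 to 40 points, and for effects from 12 points upwards it is reasonable at SD 15. What remains is that it is not supported at the protocol's own relevance threshold.

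**SD 15 is declared as an assumption.** That is disclosure and not an error. The true SD could be smaller, so any sensitivity analysis must run both ways.

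**Conclusion.** The protocol overstates its power for the SAQ, and the passages need correcting. The 80% for 11 points holds only without net loss from 60. If losses use the full allowance, it is about 74%, and the difference detectable with 80% power is about 11.9 points. At the 10-point threshold, power is about 65% with 52 women and 72% with 60, so the claimed ability to show clinically relevant effects is not delivered there. These figures assume a two-sample t-test, SD 15 and equal groups. Among them the SD matters most: from 12.5 to 20, power for 10 points with 26 per group ranges from about 81% to 42%.

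The scope is limited. The SAQ is a secondary endpoint of a pilot trial, and the CFVR sample size of 26 per group is unaffected. The difference between four scales scored 1-100 and five scored 0-100 is a clerical inconsistency that changes no power figure. A reader might also fault the protocol for not naming the scale to which the power refers, but that choice is normally left to the statistical analysis plan, which is not at hand.

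**What to change.** In the Sample size section:

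1. Replace the SAQ power claims with: *If SD is 15, 60 evaluable women give 80% power for 11 SAQ points and 72% for 10; 52 evaluable women give 80% power for about 12 points, 74% for 11 and 65% for 10.*
2. Because SD 15 was assumed without data, add a sensitivity statement in both directions for 26 per group: *Power for 10 points is about 81% if SD is 12.5 and about 42% if SD is 20, where the difference detectable with 80% power is 15.8 points.*
3. Delete the phrase about a moderate or larger effect, or define moderate in points.
4. Delete the sentence that expects power for clinically relevant effects, or limit it to the differences for which it holds.
5. Reconcile the number of SAQ scales and their range with the Seattle Angina Questionnaire section.

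The cost is wording only. No sample size, visit or measurement changes. The price is a less favourable stated power for a secondary endpoint.

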## Secondary endpoints

• Changes in symptom burden assessed by the Seattle Angina Questionnaire (SAQ)

• Changes in biomarkers including inflammatory markers and markers of metabolism

• Changes in exercise capacity (VO_2_peak)

• Changes in body weight and fat distribution (DEXA scan)

• Changes in level of anxiety and depression (HADS questionnaire)

• Changes in systolic and diastolic heart function at rest and during stress including advanced imaging (eg. Strain-Echocardiography)

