## Figure 3. Project plan milestones

## Study participants

### Inclusion criteria

Patients will be recruited and included from the ongoing iPower study (please see figure 2)^28^ i.e.

- - Female gender
  - 40-75 years of age
  - Referred to a cardiac centre for assessment with coronary angiography due to chest pain or other signs of ischemia leaving out ST-segment elevation myocardial Infarction (STEMI) or NSTEMI patients (elevated enzymes, electrocardiographic (ECG) changes/no ECG changes)
  - No significant stenotic lesions at the following CAG defined as > 50% stenosis of epicardial vessels. Patients are included from the PATS database within 1 year after coronary angiography.
- Angina with a symptom burden of symptoms > monthly
- Impaired coronary microvascular function, defined as a TTDE measured CFVR < 2.5 with a good quality (quality index > 3)
- BMI > 25 (for BMI < 26 waist hip ratio must be > 0.8)
- Informed consent

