## Blinding

- Blinding of participants and investigators to treatment allocation is not possible due to the study setup.
- All baseline assessments will be conducted before randomization.
- Reading of the primary outcome CFVR and TTSDE at follow-up will be blinded.
- VO_2_max test at follow-up will be blinded to the conducting physiotherapist.
- DEXA scan at follow-up will be blinded to the conducting MD.

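### The SAQ comparison is sized without baseline adjustment and the only SAQ model stated omits the baseline score, so a free gain in precision on a secondary endpoint is forgone

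*Protocol*

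**What the plan says.** The Sample size section gives a power statement for a between-arm SAQ comparison: 60 participants, 80% power, two-sided 0.05, "if the true difference between treatments is 11". It adds: "This is based on the assumption that the standard deviation of the response variable is 15". It does not say whether the response variable is the change in score or the week-24 score.

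The same section then states one inferential model that involves the SAQ: "Regression analysis will be performed with the primary outcome change in symptoms (SAQ) and the independent variable change in CFVR". It names no baseline covariate and no arm term, and gives no power for the slope. It also reports that the authors found no data on within-subject variation of the SAQ.

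Elsewhere, Table 1 schedules the SAQ at week 0 and week 24. The Blinding section says: "All baseline assessments will be conducted before randomization". The SAQ section says: "Scale scores are transformed to a 0-100 range". The entry criterion for symptoms is "Angina with a symptom burden of symptoms > monthly", with no limit on the starting SAQ score. Change in SAQ is listed under Secondary endpoints; the primary endpoint is change in CFVR.

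**The concern.** The baseline score of a repeated questionnaire usually predicts both the follow-up score and the change. On a bounded scale with a broad entry criterion, women with low starting scores have more room to gain than women with high ones, and regression to the mean adds to this. With equal variances at both visits, baseline and change correlate at −√((1 − rho)/2). At rho = 0.5 that is −0.5, so baseline accounts for 25% of the variance of change. An analysis of raw change leaves that share in the error term.

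Baseline SAQ is measured before allocation, so it is a valid covariate for the arm comparison and costs nothing to collect. The Aims section asks for improvement in both angina and microvascular dysfunction, so the precision of the SAQ result matters even though it is secondary. In a trial of 60, a chance imbalance in baseline SAQ would also carry partly into the difference in raw change. With equal variances the expected carry-over is (1 − rho) times the imbalance, in the opposite direction.

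**Working it through.** **Inputs from the protocol (Study design and Sample size):** difference 11, SD 15, 60 women randomized 1:1 (30 per arm), two-sided 0.05.

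**Assumptions:** the correlation rho between baseline and week-24 SAQ is not given, so a range is shown. Variances at the two visits are taken as equal.

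**1. The plan's own figure.** The standard error of the difference is 15 × √(2/30) = 3.87, so the noncentrality is 11/3.87 = 2.84. With 58 degrees of freedom, two-sided t-test power is 0.798 (0.811 by the normal approximation). The stated 80% is reproduced.

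**2. ANCOVA if 15 is the SD of change.** With visit variance σ², raw change has variance 2σ²(1 − rho) and the ANCOVA residual has variance σ²(1 − rho²). The ratio is (1 + rho)/2, so the residual SD is 15 × √((1 + rho)/2). Power uses 30 per arm and one degree of freedom fewer.

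| rho | Residual SD | Power, raw change | Power, ANCOVA | Gain (points) |
|---|---|---|---|---|
| 0.3 | 12.1 | 0.798 | 0.934 | 14 |
| 0.5 | 13.0 | 0.798 | 0.897 | 10 |
| 0.7 | 13.8 | 0.798 | 0.857 | 6 |
| 0.9 | 14.6 | 0.798 | 0.817 | 2 |

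**3. ANCOVA if 15 is the SD of the follow-up score.** The SD of change is then 15 × √(2(1 − rho)) and the ANCOVA residual SD is 15 × √(1 − rho²). The endpoint is change, so the right comparator is the change-score analysis at the same rho.

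| rho | SD of change | Power, raw change | ANCOVA SD | Power, ANCOVA | Gain (points) |
|---|---|---|---|---|---|
| 0.3 | 17.75 | 0.656 | 14.31 | 0.833 | 18 |
| 0.5 | 15.00 | 0.798 | 12.99 | 0.897 | 10 |
| 0.7 | 11.62 | 0.950 | 10.71 | 0.974 | 2 |

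Under both readings the ANCOVA residual SD is below 15, so the 11-point, SD 15 statement is conservative for an ANCOVA.

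**4. The regression of SAQ change on CFVR change.** No slope, correlation or power is stated, so there is no figure to reproduce. If baseline SAQ is unrelated to CFVR change, adding it multiplies the standard error of the slope by about √((1 + rho)/2). At rho = 0.5 this is √0.75 = 0.87, a fall of about 13%. If baseline SAQ is related to CFVR change, that figure does not apply and the adjusted slope estimates a different quantity.

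**The case against.** The strongest reply is that a covariate list is commonly left to a statistical analysis plan, and none is at hand. The quoted sentence names an outcome and an independent variable; it does not say the model is unadjusted or rule out further terms. That is fair, and nothing here is stated wrongly. What remains is that the section does fix a specific model on raw change and an unadjusted sizing, and a better method is available from data already scheduled.

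A reader might infer several stronger things, which the documents do not support:

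- **That the plan loses about 10 points of power.** This needs rho near 0.5, which the protocol does not give. The planned 80% is met without adjustment, so the gain is forgone, not lost.
- **That this gain belongs to the quoted regression.** It belongs to the between-arm difference of 11 points. The regression is an association model with no arm term and no stated power.
- **That a baseline term removes ceiling effects.** A linear covariate does not undo the bound of a 0–100 scale, and the protocol gives no baseline SAQ distribution to show how many women start near the top.
- **That adjustment costs only one degree of freedom.** This is so for the randomized comparison. CFVR change is not randomized, so in that regression conditioning on baseline SAQ can change the slope itself.

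**Conclusion.** The point holds as a forgone gain in precision on a secondary endpoint of a pilot trial. The stated power figure is right: 0.798 for SD 15 and 30 per arm. Baseline adjustment of the between-arm comparison would add about 14 to 2 points of power over rho 0.3 to 0.9 if 15 is the SD of change. It would add about 18 to 2 points over rho 0.3 to 0.7 if 15 is the SD of the follow-up score and raw change is the comparator.

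These sizes rest on equal variances at both visits and on an assumed rho. For the SAQ–CFVR slope, the only size that can be given is the conditional 13% fall in standard error at rho = 0.5. The change is worth making because it is nearly free. Validity of the planned comparison does not depend on it.

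**What to change.** In the analysis paragraph of the Sample size section:

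1. State that the between-arm SAQ comparison will be an ANCOVA of the week-24 score on arm and the baseline score of the same SAQ scale. Keep the 11-point, SD 15 power statement and describe it as conservative. Say whether 15 is the SD of change or of the follow-up score.
2. Report the regression of SAQ change on CFVR change with baseline SAQ as a covariate as well. Note that no power is stated for this slope, that its standard error falls only if baseline SAQ is unrelated to CFVR change, and that otherwise adjustment also changes the slope being estimated.

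The cost is a few sentences of analysis wording. No new data and no additional participants are needed, and the between-arm comparison gives up one degree of freedom.
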